## Abstract

**Background:**

The burden of dengue continues to increase globally, with an estimated 100 million clinically apparent infections occurring each year. Although most dengue infections are asymptomatic, patients can present with a wide spectrum of clinical symptoms ranging from mild febrile illness through to severe manifestations of bleeding, organ impairment, and hypovolaemic shock due to a systemic vascular leak syndrome. Clinical diagnosis of dengue and identification of which patients are likely to develop severe disease remain challenging. This study aims to improve diagnosis and clinical management through approaches designed a) to differentiate between dengue and other common febrile illness within 72 h of fever onset, and b) among patients with dengue to identify markers that are predictive of the likelihood of evolving to a more severe disease course.

**Method/Design:**

This is a prospective multi-centre observational study aiming to enrol 7–8000 participants aged ≥ 5 years presenting with a febrile illness consistent with dengue to outpatient health facilities in 8 countries across Asia and Latin America. Patients presenting within 72 h of fever onset who do not exhibit signs of severe disease are eligible for the study. A broad range of clinical and laboratory parameters are assessed daily for up to 6 days during the acute illness, and also at a follow up visit 1 week later.

**Discussion:**

Data from this large cohort of patients, enrolled early with undifferentiated fever, will be used to develop a practical diagnostic algorithm and a robust clinical case definition for dengue. Additionally, among patients with confirmed dengue we aim to identify simple clinical and laboratory parameters associated with progression to a more severe disease course. We will also investigate early virological and serological correlates of severe disease, and examine genetic associations in this large heterogeneous cohort. In addition the results will be used to assess the new World Health Organization classification scheme for dengue in practice, and to update the guidelines for “Integrated Management of Childhood Illness” used in dengue-endemic countries.

**Trial registration:**

NCT01550016. Registration Date: March 7, 2012

## Background

Dengue is an arboviral disease caused by infection with any one of four related dengue virus (DENV) serotypes. It is currently the most important mosquito-borne viral pathogen affecting humans, and is emerging as a major threat to global health. Best estimates indicate that some 3 billion people live in parts of the world where they are at risk of infection and that around 96 million symptomatic episodes and approximately 20,000 deaths occur each year [1]. As yet, neither vaccines nor specific therapies are available although both areas are currently the focus of intense research efforts.

Among symptomatic dengue cases a wide variety of clinical manifestations are seen, ranging from mild febrile illness to severe and potentially fatal disease. Only a small proportion of patients progress to more severe disease, typically manifesting with a transient systemic vascular leak syndrome around the time of defervescence; plasma leakage occurs, usually accompanied by altered haemostasis and thrombocytopenia [2]. Leakage may be profound, particularly in children, sometimes resulting in life-threatening dengue shock syndrome (DSS). Other severe complications, such as severe liver, cardiac or neurological involvement, may also occur but are less frequent. With expert supportive care mortality rates have been reduced to very low levels, in many centres of excellence down to less than 1 % for those with severe disease [3]. Careful observation and judicious use of intravenous fluid therapy are crucial, with urgent shock resuscitation required in only a small proportion of cases. However, a major issue for clinicians treating such patients remains the fact that clinical diagnosis of dengue is difficult in the early febrile phase of the illness without reliance on expensive diagnostics. Secondly prediction of risk for the development of complications such as shock due to systemic vascular leak syndrome is currently poor. As a result very large numbers of patients with possible dengue, potentially at risk for severe disease, are admitted to higher level healthcare facilities in endemic areas primarily for observation, overburdening the system such that the often limited local resources are not used to maximal advantage for those patients who do need expert care.

### Clinical features and warning signs

Two major clinical syndromes, dengue fever (DF) and dengue haemorrhagic fever (DHF), were first described 50 years ago in Thailand, with case definitions and management guidelines published by the World Health Organization (WHO) in the 1970s [4]. However, practical limitations with this classification system have become increasingly apparent, and a growing body of evidence indicates that the two syndromes are part of a continuous spectrum of disease rather than being discrete entities [5–8]. As a result a revised classification system has been developed, based in part on prospectively collected data from over 2000 patients recruited across seven endemic countries (DENCO study), which was adopted in the revised WHO dengue guidelines published in 2009 [9, 10]. The new scheme classifies the disease more simply into dengue and severe dengue, with the hope that this will prove more effective for triage and clinical management, and will also improve the quality of surveillance and epidemiological data collected globally.

Dengue and other febrile illnesses (OFI) share many clinical features (e.g. headache, myalgia, rash), and most countries where dengue is common also have epidemics of illnesses such as measles, typhoid, leptospirosis and influenza that are easily confused with dengue in the early phase. Although a case definition for dengue fever has been included in the WHO guidelines for many years [11, 12], in view of the variability in clinical presentation laboratory confirmation is considered desirable. However for many endemic countries this is not a feasible option, and simple and inexpensive strategies that rely on clinical and/or readily available laboratory parameters to provide a reliable early diagnosis are needed. Clinical warning signs suggestive of likely progression to severe dengue are also included in the new guidelines, but the evidence from the DENCO study in support of specific warning signs was limited by the small numbers of patients who progressed to the severe category while under observation. Thus, although warning signs are considered a key component for early recognition of potentially severe disease, the current evidence for any clinical/laboratory markers is weak. Further research is need to determine whether clinical/laboratory warning signs with high predictive power can indeed be identified, but to do this a very large cohort of patients needs to be assessed from the early febrile phase, in order to capture sufficient patients who progress to more severe disease.

### Pathogenesis

Despite intensive efforts dengue disease pathogenesis remains incompletely understood, particularly in relation to the mechanisms responsible for the systemic vascular leak syndrome [13]. It is clear that although all four viral serotypes can cause fatal disease, second or subsequent infections are much more likely to be associated with severe clinical manifestations than primary infections [14, 15]. There is also evidence to suggest that severe disease is associated with higher plasma viremia, and to implicate immune response mechanisms to the virus as playing a significant role in pathogenesis [16, 17]. However, data on plasma viremia in primary versus secondary infections and/or in relation to disease severity are inconsistent, and detailed examination of viremia kinetics has been limited to date, with the focus primarily on hospitalised patients [18–20].

Dengue non-structural protein (NS1) is a glycoprotein expressed by dengue-infected cells [13, 21, 22]. The availability of commercial antigen-capture assays that detect NS1 in plasma or serum presents an opportunity for it to be used for early and rapid dengue diagnosis. It has also been proposed as a prognostic marker for severe disease [23]. Numerous studies have confirmed NS1 to be highly specific for dengue, but sensitivity has been variable according to the serotype involved, the geographical location, the immune status of the patient, and the day of illness on testing [24, 25]. Since it is crucial to understand the limitations of such tests before they can be recommended for routine use in the community, large, well-powered studies that can determine the true sensitivity and specificity of NS1 testing in real world settings are essential.

Dengue virus reactive IgG antibodies are also considered to play a critical role in determining risk for severe dengue via processes such as virus neutralisation and/or infection enhancement [26]. However, despite their importance the features of polyclonal sera that are associated with development of severe dengue have not been characterised as yet. Finally, although genetic predisposition to dengue has long been suggested, almost every study on this topic has been underpowered, did not consider population stratification, and did not go on to replicate the findings in independent patient cohorts. In the first genome-wide case–control genetic association study performed in dengue, several SNPs associated with DSS that are significant at the genome-wide level were identified, the most striking associations being SNPs in the MICB and PLCE1 genes [27]. Genetic variants of MICB and PLCE1 have also been found to be associated with less severe forms of dengue, and also dengue in infants [28]. Validation that these SNPs are associated with a) clinically apparent dengue (as distinct from DSS) in patients from other Asian and also Latin American countries and b) the magnitude of viremia or NS1 concentration in the early febrile period are required.

In summary, the pathological mechanisms associated with severe dengue remain obscure, and the crucial question of exactly how the virus causes the serious complications observed in patients remains unanswered.

### Primary objectives

The study aims to improve diagnosis and clinical management of dengue through approaches designed a) to differentiate between dengue and other common febrile illness within 72 h of fever onset, and b) among patients with dengue to identify markers that are predictive of the likelihood of evolving to a more severe disease course.AIM 1: To identify clinical and/or simple laboratory parameters which differentiate between dengue and non-dengue illness within the first 72 h of fever, with the overall aim of developing a robust case definition for dengue.AIM 2: To identify clinical and/or simple laboratory parameters among dengue infected patients that predict likely progression to a more severe disease course.AIM 3: To identify virological correlates of severe dengue – in particular to assess plasma viremia and NS1 antigenemia within the first 72 h of fever in patients with confirmed dengue.AIM 4: To identify early serological correlates of severe dengue, in order to characterize differences between severe and uncomplicated disease.

### Secondary Objectives

AIM 1: To evaluate practical application of the original (WHO 1997) and the new dengue classification schemes (WHO 2009) across a series of clinical sites.AIM 2: To use the data to update the guidelines for “Integrated Management of Childhood Illness” used in dengue-endemic countries.

## Methods/Design

This is a prospective multi-centre observational study aiming to enrol 7 to 8,000 patients presenting with a febrile illness consistent with a diagnosis of dengue to outpatient health facilities in urban centres in 8 countries across Asia and Latin America. The study is coordinated centrally by the Section Clinical Tropical Medicine in Heidelberg, Germany, and the Oxford University Clinical Research Unit (OUCRU) in Ho Chi Minh City (HCMC), Vietnam. The countries participating in the study, and the centres coordinating the work locally in each country, are indicated in Table 1. The study is being performed in accordance with ICH-GCP guidelines, with regular oversight by a team of independent monitors.

**Table 1 Tab1:** Countries/centres enrolling participants into the study

Coordinating Centre	City, Country	Ethics Committees Involved
Heidelberg University Hospital	San Salvador, El Salvador	• Comité de Ética en Investigación Clínica (CEIC), Hospital Nacional de Niños Benjamín Bloom, San Salvador, El Salvador
Ethics Committee, Faculty of Medicine, Heidelberg University	Fortaleza, Brazil	• Comitê de Ética em Pesquisa da Universidade Estadual do Ceará (CEP-UECE), Fortaleza, Brazil • Comissão Nacional de Ética em Pesquisa (CONEP), Brasília, Brazil
	Recife, Brazil	• Comitê de Ética em Pesquisa do Centro de Pesquisas Aggeu Magalhães (CEP-CPqAM) • Comitê de Ética em Pesquisa em Seres Humanos do Instituto de Medicina Integral [name] (CEP-IMIP), Recife, Brazil • Comissão Nacional de Ética em Pesquisa (CONEP), Brasília, Brazil
	Rio de Janeiro, Brazil	• Instituto de Pesquisa Clínica Evandro Chagas (IPEC), Fundação Oswaldo Cruz (Fiocruz), Rio de Janeiro, Brazil • Comissão Nacional de Ética em Pesquisa (CONEP), Brasília, Brazil
	Maracay, Venezuela	• Comité de Bioética del Instituto de Investigaciones Biomédicas de la Universidad de Carabobo, Maracay, Venezuela
	Dhaka, Bangladesh	• Ethical Review Committee, International Centre for Diarrhoeal Disease Research, Dhaka, Bangladesh
Oxford University Clinical Research Unit – Viet Nam	Yogyakarta, Indonesia	• Medical and Health Research Ethics Committee, Faculty of Medicine, Gadjah Mada University, Yoygakarta, Indonesia
Oxford Tropical Research Ethics Committee (OxTREC)	Siem Reap, Cambodia	• Institutional Review Board, Angkor Hospital for Children, Siem Reap, Cambodia

### Study population and patient enrolment

Both adults and children (≥5 years) are eligible for enrolment, and it is anticipated that the relative proportions will reflect the expected local dengue epidemiology in each country. Following appropriate informed consent, subjects presenting to outpatient departments (OPD) at the designated sites with fever for ≤ 72 h without localizing features, i.e. consistent with a possible diagnosis of dengue, are being enrolled.

### Inclusion criteria

Any patient presenting to the OPD at the participating centres is eligible for enrolment if they meet the following criteria:Age ≥ 5 yearsFever or history of fever for ≤ 72 hClinical symptoms consistent with possible dengue – i.e. suspected dengue and/or undifferentiated fever in a patient from a dengue endemic areaConsidered by the treating physician to be suitable for outpatient care at the time of study enrolment – i.e. no signs of severe diseaseWritten informed consent

### Exclusion criteria

Localizing features suggesting an alternative diagnosis, eg pneumonia, otitis etc.The physician judges that the patient is unlikely to attend daily follow up - e.g. due to travelling distance from the clinicAt each OPD a triage system has been established to direct potentially eligible subjects to a selected outpatient room/area for consideration for enrolment, where study staff are available to assist the regular clinic staff in patient enrolment and collection of data. The study staff discuss the study with all potential adult participants or, in the case of children 5–17 years of age accompanied by a parent/guardian, with the accompanying parent/guardian. Study staff describe the purpose of the study, the study procedures, possible risks/benefits, the rights and responsibilities of participants, and alternatives to enrolment, and provide a written Patient Information Sheet. If the patient or parent/guardian agrees to participate, they are asked to sign an Informed Consent Form, a copy of which is then given to them to keep. If the patient or parent/guardian is indecisive about enrolment, they are given as much time as necessary to consider the study up until 72 h of illness has passed at which point the patient/child is no longer eligible for the study. Children aged 12–17 are also asked to give assent to the study, after discussion with study staff and having their questions answered. A separate Assent Form is provided, for the child to sign with a copy for them to keep. In addition to the procedures above, illiterate signatories have the Informed Consent/Assent Form read to them in the presence of a witness who signs to confirm this. All Patient Information Sheets and Consent/Assent forms are written in the local language and use terms that are easily understandable.

### Data collection instrument

A structured clinical questionnaire is completed upon enrolment and then once daily for up to six days for all patients in the study. This case report form (CRF) includes detailed clinical signs and symptoms, as well as all standard laboratory results. Data collection focuses in particular on recording the timing of onset of new signs or symptoms, and on assessing the severity of symptoms in a systematic way (mild/moderate/severe). The final format was agreed by the Principal Investigators at the participating clinical centres prior to translation into relevant languages for local use. The CRF is supported by a series of standard operating procedures (SOPs) describing in detail all study procedures, severity definitions and methods for documentation, and all SOPs are also presented in the appropriate local language.

### Clinical evaluation

Following enrolment clinical history and examination findings are recorded in the CRF, and a 3–5 ml (age-dependent) research blood sample is obtained, together with appropriate samples to measure a range of haematological and biochemical parameters following local laboratory requirements (Table 2). Patients are then reviewed daily in the OPD until fully recovered and afebrile for 24 h, or for up to 6 days from enrolment. A rapid access card is provided to each study participant to facilitate these daily visits. Standardized clinical information is recorded and a full blood count is performed at each visit, plus any other tests deemed necessary by the clinic physician. On the last acute illness visit (within approximately 24 h of defervescence) a second sample for a biochemical profile is obtained together with a sample for serology. All patients are then asked to attend a final follow-up visit around day 10–14 of illness, at least one week from the last visit during the acute illness. In addition to a clinical assessment at this time a last blood sample is taken for convalescent serology and a full blood count.

**Table 2 Tab2:** Blood sample collection - schedule and volumes

	Test	Enrolment (≤72 h fever)	Daily for up to 6 days	Final acute visit	Follow-up, Day 10-14
Research	Dengue NS1 Dengue IgM/G DENV PCR Serological & virological and/or genetic studies	3 ml EDTA for children 5 ml EDTA for adults		2 ml EDTA	2 ml EDTA
Haematology	Full blood count	1 ml EDTA	1 ml EDTA	1 ml EDTA	1 ml EDTA
Biochemistry	AST/ALT Albumin Creatine kinase Creatinine	2 ml Lithium Heparin^a^		2 ml Lithium Heparin^a^	

^a^or serum/an alternative additive according to local laboratory requirements

All management decisions throughout the acute illness are at the discretion of the clinic physicians. Any patient requiring hospital admission continues to be followed daily using a similar but more detailed CRF, with the indication(s) for admission clearly documented, and all management interventions recorded together with the physician’s rationale for these interventions.

### Laboratory evaluation

Haematology and biochemistry profiles are performed on standard laboratory instruments at the various participating sites, with evidence for quality assurance and quality control checked by study monitors at regular intervals.

NS1 antigen detection (Platelia NS1, Biorad) and diagnostic serological assays (IgM and IgG Capture ELISA Kits, Panbio, Australia) are being performed in batches at a designated laboratory in each country, or at the OUCRU laboratory in HCMC if in-country diagnostics are not feasible. Proficiency panels were used to assess the capacity of each site to perform the assays in an appropriate manner before the study commenced. NS1 detection is attempted on all enrolment plasma samples, while diagnostic serology is performed on acute and convalescent plasma samples (follow-up visit specimen if available, or final acute visit specimen if not).

Plasma viremia levels are measured in designated centres on enrolment plasma samples by qRT-PCR using a validated assay. Samples from all sites in Vietnam, Cambodia, Malaysia, Bangladesh, and El Salvador are being assayed at the OUCRU laboratory in HCMC. The research laboratory at the Gadjah Mada University is responsible for the Indonesian diagnostics, while specimens from the remaining sites in Latin America will be assayed at the FIOCRUZ Laboratories in Recife and Rio de Janeiro, or at the Institute Pedro Kouri in Havana, Cuba. Harmonization of assay protocols, reagents and equipment has been performed to ensure equivalence between the laboratories. A single diagnostic database is maintained in HCMC, where data from all sites are collated and checked for errors/inconsistencies following a formal data validation SOP.

For the detailed serological research studies, a range of high-throughput functional and serological assays will be considered for the measurement of DENV-specific antibodies. The intention of the serological studies will be to understand whether the quality and quantity of the anti-DENV antibody response differs between patients with mild versus severe clinical or laboratory outcomes.

### Case definitions

Laboratory diagnosis of a dengue case will be in accordance with current WHO criteria [9]. The diagnostic algorithm is shown in Fig. 1. Briefly, any case with virological evidence of dengue as shown by a positive RT-PCR assay or NS1 ELISA test, or who has IgM seroconversion between paired specimens, is defined as having laboratory-confirmed dengue. A diagnosis of OFI is assigned to participants with no laboratory evidence of acute or recent dengue. Among participants with confirmed dengue a probable primary infection is defined by negative IgG Capture results on both the enrolment and follow-up samples, while a probable secondary infection is defined by a positive IgG Capture result in either or both the enrolment and follow-up samples.

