#### Sample size

We anticipate that dengue will be confirmed in ~ 50 % of the patients enrolled in Asia and ~ 20–30 % of the patients enrolled in Latin America. We also expect to make a definite negative diagnosis – i.e. that the patient did not have dengue – in at least 80 % of the remaining patients. Among hospitalised patients enrolled in previous descriptive studies in Vietnam around 5 % of cases progressed to severe disease; there is currently no data available for patients managed in the community but the progression rate is likely to be lower. In this study, among patients with confirmed dengue we will use two definitions of more severe disease: 1) severe dengue as defined in the new WHO 2009 classification scheme and 2) the combined endpoint of hospitalization or IV fluid administration or severe dengue. From a total enrolment of 7–8,000 cases we anticipate that around 3,000 dengue cases will be included in the cohort, potentially with 100–150 patients progressing to severe disease, primarily dengue shock syndrome. Hospitalization and/or IV fluid administration are likely to be considerably more common but will vary according to resources available and local clinical guidelines; however it seems plausible that the *relative* effect of risk factors on outcome will be similar across countries and regions. A dengue cohort of this size should allow for the assessment of up to 15 candidate risk factors even for the less frequent outcome of severe disease.

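### OFI and probable primary infection rest on negative serology, yet an early final acute specimen may stand in for the day 10–14 sample with no timing condition, so late seroconverters can be mislabelled

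*Protocol article*

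**What the plan says.** The relevant rules are spread over four sections of the Protocol article.

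- **Case definitions.** Confirmed dengue requires "virological evidence of dengue as shown by a positive RT-PCR assay or NS1 ELISA test, or who has IgM seroconversion between paired specimens". Among patients not confirmed, "A diagnosis of OFI is assigned to participants with no laboratory evidence of acute or recent dengue". Among confirmed cases, "a probable primary infection is defined by negative IgG Capture results on both the enrolment and follow-up samples", and a positive IgG on either sample makes the infection probable secondary.
- **Laboratory evaluation.** PCR and NS1 use the enrolment plasma. For serology, the later specimen is the "follow-up visit specimen if available, or final acute visit specimen if not". The Fig. 1 caption also describes the second sample (S2) as either follow-up or early convalescent.
- **Clinical evaluation.** Patients are reviewed daily "until fully recovered and afebrile for 24 h, or for up to 6 days from enrolment". "On the last acute illness visit (within approximately 24 h of defervescence) a second sample for a biochemical profile is obtained", together with a serology sample. The later visit is placed "around day 10–14 of illness, at least one week from the last visit during the acute illness".
- **Sample size.** "We also expect to make a definite negative diagnosis" in at least 80% of those not confirmed.

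The text gives no minimum illness day or S1–S2 interval for a negative pair. It names no class for a negative pair whose second member is the final acute specimen.

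**The concern.** A positive result on an early second specimen is informative. A negative one may only mean that antibody has not yet risen. Read together, the sections let that early negative count in the same way as a negative at day 10–14.

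Two labels are exposed, to different degrees:

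- **Probable primary.** Every confirmed case is typed by IgG alone, so a positive PCR or NS1 gives no protection. One missed IgG rise turns a secondary infection into a primary one. The Pathogenesis section links second and later infections to more severe illness, so an error here could blur any severity comparison that uses this status.
- **OFI.** This is the comparison group for the case definition in primary Aim 1. A missed dengue case in it would weaken the apparent discrimination of any diagnostic model.

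**Working it through.** **1. The plan's own figures.** About 40% of 7,500 (the midpoint of 7,000–8,000) is 0.40 × 7,500 = 3,000 dengue cases, as stated. The interim share is 2510/5996 = 41.9%, stated as 42%. Neither figure is in dispute.

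**2. Timing.** Enrolment is at most 72 h into fever and acute review lasts at most 6 days, so the fallback specimen falls at about illness day 3 + 6 = 9 at the latest. A history of fever is enough for entry, and review stops after recovery and 24 h without fever. In a patient who recovers fast, the fallback can therefore come within a few days of enrolment. The scheduled specimen comes at least a week after the final acute visit.

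**3. The not-definite group.** Those not confirmed number 7,000 − 3,000 = 4,000 to 8,000 − 3,000 = 5,000. At least 80% definite means 3,200–4,000 or more, which leaves up to 800–1,000 not definite.

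**4. Dengue labelled OFI.** Four things must coincide: negative PCR, negative NS1, no follow-up specimen, and no IgM rise by the final acute visit. The document gives none of these rates, so all are assumed, and independent of each other:

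- v, share of dengue negative on both PCR and NS1: 5–20%
- f, share without a follow-up specimen: 5–30%
- m, share not yet IgM-positive at the final acute visit: 25–75%

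Number mislabelled = 3,000 × v × f × m, compared with an OFI group of 3,200–4,000:

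- Low: 3,000 × 0.05 × 0.05 × 0.25 ≈ 2, about 0.05%
- Middle: 3,000 × 0.10 × 0.20 × 0.50 = 30, or 30/4,000 to 30/3,200 = 0.75–0.94%
- High: 3,000 × 0.20 × 0.30 × 0.75 = 135, or 135/4,000 to 135/3,200 = 3.4–4.2%

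**5. Secondary infection labelled primary.** Let s be the true secondary share among confirmed cases (assumed 50–80%), f as above, and n the share of secondary infections still IgG-negative on the early pair (assumed 10–50%). True primary infections are taken to stay IgG-negative.

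False share of primary labels = s·f·n / (1 − s + s·f·n):

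- Low (s 50%, f 5%, n 10%): 0.0025/0.5025 = 0.5%, about 8 of 3,000
- Intermediate (s 70%, f 20%, n 25%): 0.035/0.335 = 10.4%, 105 cases
- High (s 80%, f 30%, n 50%): 0.12/0.32 = 37.5%, 360 cases

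The result is sensitive to s alone. With f 15% and n 40%, s = 75% gives 0.045/0.295 = 15%, and s = 50% gives 0.03/0.53 = 5.7%.

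**The case against.** The best defence is that the visible text is a summary. Case definitions says that it gives the algorithm briefly and points to Fig. 1, which is not available here. The Sample size section expects a definite negative in only part of the unconfirmed group, so a not-definite class is foreseen, and Fig. 1 or a separate procedure may define it. The Laboratory evaluation rule can also be read as saying only which specimens are assayed, not how a negative pair is classed. Taken literally, the primary definition asks for a follow-up sample, and both infection labels are called probable. The article also defers detailed analysis plans to other documents.

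Much of this stands, and it rules out several stronger readings:

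- A reader might infer that patients *are* mislabelled. The text shows only that they *can* be if the rule is followed as worded.
- A reader might infer that the Aim 1 reference standard is seriously contaminated. PCR and NS1 limit this, and the figures in step 4 are small.
- A reader might infer that primary/secondary status is a planned key covariate for Aims 2–4. No aim or analysis section names it; it appears as background and as a case definition.
- A reader might infer that the error follows severity, because mild cases skip follow-up. This is plausible, but the document says nothing about who misses the visit, and it excludes patients judged unlikely to attend daily review.

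The defence does not remove the gap itself. The article states a working substitution rule and working definitions. A negative pair that rests on an early fallback contains no evidence of dengue, so by the wording it is OFI. The Fig. 1 caption accepts an early convalescent sample without a time condition.

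**Conclusion.** The point holds as a conditional one. As worded, the rules allow late seroconverters without a day 10–14 specimen to be labelled OFI or probable primary.

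The primary/secondary label carries most of the exposure. The false share of primary labels runs from 0.5% to 37.5% across the assumed inputs, which means that its size is unknown rather than shown to be large. The OFI effect is about 1% or less in middle scenarios and about 4% at most. All these sizes rest on assumed rates of missing follow-up, virological negativity and delayed antibody rise. Fig. 1 may already settle part of the matter, so no mismatch between text and figure can be claimed.

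**What to change.** Reconcile Case definitions, Laboratory evaluation and Sample size in one statement:

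1. Keep any positive result as valid, whichever specimen it comes from.
2. Assign OFI and probable primary only when the negative second specimen meets a minimum illness day or S1–S2 interval fixed before analysis. The day 10–14 specimen meets it, and a late final acute specimen may. Rejecting every fallback pair would be too blunt, since some fall near illness day 9.
3. Class other negative pairs as indeterminate, in keeping with the definite-negative share that the Sample size section expects.
4. For OFI versus dengue, report results with indeterminate patients counted as OFI, counted as dengue, and excluded or multiply imputed. Add an analysis restricted to patients with the day 10–14 specimen.

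The cost is new wording and a reclassification in the existing diagnostic database, with no new tests. The downside is fewer firmly classified patients. As an upper illustration, suppose 20% lack follow-up (assumed) and every fallback pair fails the timing rule. Then up to 0.20 × 4,000 to 0.20 × 5,000 = 800–1,000 unconfirmed patients become indeterminate, which is the number the Sample size section already allows for. With s 70% and n 25%, 105 + 0.20 × 900 = 285 of 3,000 confirmed cases would lose a firm primary label. Accepting late final acute specimens lowers both numbers.
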